### Primary Analyses

The unit of analysis is the participant. Because the motor subscale of the FONEFIM, a continuous variable, is measured at baseline, 3-, and 6-months, we will use a linear mixed-effects model. Fixed effects in the model will include treatment (TR or Usual Care), RBU, (with or without), time (3-and 6 -months), and the interactions between treatment and RBU and between treatment and time. Participant level random effects (e.g., patient age; stroke severity; elapsed time between stroke onset and enrollment in the study) will be included in the model to account for correlations between participants' repeated measures over time. Primary analyses will be conducted as intent-to-treat, and sensitivity analyses will examine the implications of the intent-to-treat assumption.

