#### Control Variables

Sociodemographic variables (age, sex, race, education, income, marital status, and number of people living with the participant) are collected via self-report. Several clinical variables are collected at baseline as well. Stroke severity is measured by the Goldstein and Chilukuri scale, which is an algorithm to derive the Canadian Neurological Scale (CNS) retrospectively based on information in the patient's medical record [38]. The CNS, a highly reliable and valid stroke scoring system [39], focuses on level of consciousness, speech and strength. The aggregate physical dimension score from the Stroke Impact Scale (SIS) 2.0 is used at baseline to assess stroke related physical impairment [40]. The physical dimension score is a composite of four primary SIS domains: strength, hand function, ADL/IADL and mobility. The SIS uses a 5-point Likert scale ranging from "not difficult at all" to "cannot do at all." The Geriatric Depression Scale (GDS) is employed to measure depression [41]. The GDS is a 30-item scale, where each item is measured on a "yes/no" format. Scores range from 0 to 30, with higher values reflecting greater levels of depression.

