### Sample Size Determination and Statistical Power

The primary research question is: Over the study period, does the TR group have greater improvement in function (motor sub-scale of the FONEFIM) than the Usual Care group?

In our sample size calculations, we assume a standardized difference of 0.50 in the motor FIM score from baseline to 6 months, based on a randomized trial of a combination of assistive technology and exercise intervention similar to our study, that used a measure of ADL similar to the motor FIM over 6 months [42]. In a sample of 163 patients with a first ever stroke admitted for inpatient rehabilitation, Schepers et al. [42] reported a standard deviation of 8.3 for the unadjusted FIM motor domain for stroke patients. Based on a standard deviation adjusted to account for correlation between repeated measurements of the outcome, and using an independent samples t-test with a 0.05 two-sided significance level and 80% power, a sample size of 20 patients per group is required to detect a mean difference of 9.2 or higher in the FIM motor score between the intervention and control groups. Because we assume an approximate dropout rate of 20%, we are recruiting approximately 25 stroke patients per arm. We will test for baseline imbalances. If we find significant differences between the groups on baseline factors, we will control for these in secondary analyses to determine if these may account for between group differences in study outcomes.

If the proportion of drop outs are missing at random or missing completely at random, the likelihood-based mixed model for repeated measures will be applied for the data analysis. Multiple imputation techniques will also be applied to replace the missing data for both the cases that are considered to be drop outs and deaths. The results of the analyses using both the imputed and un-imputed data will be compared. If were to suspect that these analytical techniques were to yield missing not at random (MNAR) drop-out mechanisms or deaths, then we will try sensitivity analysis approaches based on the best scenario or worst scenario assumptions.

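### Baseline covariates (age, stroke severity, time since stroke) are given the job of modelling within-person correlation and left out of the fixed effects, and secondary adjustment is chosen by baseline significance tests

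*Protocol article*

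**What the plan says.** The Primary Analyses section of the protocol article plans a linear mixed-effects model for the FONEFIM motor score, which is measured at baseline, 3 and 6 months.

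- **Fixed effects:** "Fixed effects in the model will include treatment (TR or Usual Care), RBU, (with or without), time (3-and 6 -months"), plus treatment by RBU and treatment by time. No patient covariate is listed.
- **Random effects:** "Participant level random effects (e.g., patient age; stroke severity; elapsed time between stroke onset and enrollment in the study"). Their purpose is stated: they "will be included in the model to account for correlations between participants' repeated measures over time".

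Under Sample Size Determination and Statistical Power, the missing-data text says that "the likelihood-based mixed model for repeated measures will be applied for the data analysis", without giving a covariance structure. The same section says "We will test for baseline imbalances" and continues: "If we find significant differences between the groups on baseline factors, we will control for these in secondary analyses". It gives neither a test level nor a list of factors.

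The Control Variables section lists what is collected at baseline: "Sociodemographic variables (age, sex, race, education, income, marital status, and number of people living with the participant"), together with stroke severity, the SIS physical score and the GDS.

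**The concern.** Age, stroke severity and time from stroke to enrollment each take one value per person. As prognostic variables they belong in the mean of the model. A random coefficient on such a variable makes each person's correlation between visits depend on how far that person's value lies from zero, which is not the dependence that repeated measures produce. A participant intercept or a visit covariance would model it. The plan gives that job to the wrong terms, and the three variables then do nothing for the mean.

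Two things are at stake: a valid standard error for whichever treatment contrast is reported, and the precision that known prognostic factors could give a trial of about 50 people.

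The baseline tests raise a related problem. In a properly randomized trial every baseline difference is a chance difference. Choosing covariates by p-value therefore makes the adjusted secondary result depend on chance rather than on what predicts outcome.

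**Working it through.** **Inputs.** From the plan: 20 evaluable per group, 20% dropout, 25 recruited per arm (20/(1 − 0.2) = 25, which reproduces), two-sided 0.05, visits at baseline, 3 and 6 months. Assumed, because the documents do not give them: correlation 0.5 between visits (0.7 in some runs), total SD 10, covariates explaining 30% of between-person variance, baseline test level 0.05. The plan prints no error rate for this model, so there is no figure to reproduce.

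**1. What random slopes imply.** With random coefficients of variance τ²ₖ on covariates xᵢₖ and residual variance σ², person i has gᵢ = Σ τ²ₖ x²ᵢₖ and correlation gᵢ/(gᵢ + σ²).

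- Centred covariates, each τ²ₖ = σ²/3 for illustration: someone at the mean of all three has gᵢ = 0 and correlation 0; one SD away on each, gᵢ = σ² and correlation 0.5; two SD away on each, gᵢ = 4σ² and correlation 0.8.
- Uncentred age over the eligible range of 45 to 90: (90/45)² = 4, so the age component is four times as large at 90 as at 45, but nobody is near zero.

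**2. Which contrast is affected.** gᵢ is common to all of a person's visits, so it cancels from within-person change. With correlation 0.5 and SD 10, σ² = 50 and between-person variance is 50. By hand, for 25 per arm:

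- Change to 6 months: √(2 × 50 × 2/25) = 2.83.
- Average level over three visits: √((50 + 50/3) × 2/25) = 2.31.

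Null simulation by REML (25 per arm, three visits, 500 runs, correlation 0.5, RBU terms left out):

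| Terms fitted | Change to 6 months: mean SE / true SD / type I | Average level: mean SE / true SD / type I |
|---|---|---|
| Centred slopes, no intercept | 2.91 / 2.85 / 0.054 | 2.01 / 2.67 / 0.128 |
| Uncentred slopes, no intercept | 2.84 / 2.85 / 0.054 | 2.23 / 2.52 / 0.078 |
| Participant intercept only | 2.83 / 2.85 / 0.054 | 2.31 / 2.44 / 0.074 |
| Intercept plus centred slopes | 2.83 / 2.85 / 0.054 | 2.18 / 2.48 / 0.086 |
| Intercept, covariates fixed | 2.83 / 2.85 / 0.054 | 2.09 / 2.17 / 0.050 |

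In the first row the level SE is 1 − 2.01/2.67 = 25% too small. Monte Carlo error on a rate of 0.05 is about 0.01, so 0.078 and 0.074 cannot be told apart.

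**3. Post-baseline visits only** (20 per arm, 3 and 6 months, null):

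- Centred slopes, no intercept, 2000 runs, correlation 0.5, covariate R² 0 and 0.3: average effect 0.097 and 0.102; 6-month effect 0.085 and 0.079. With a participant intercept: 0.039 to 0.056.
- Standardized slopes, no intercept, 600 runs per correlation: 0.132 (correlation 0.5) and 0.135 (0.7). With an intercept: 0.055 and 0.052.
- Uncentred slopes, correlation 0.5: 0.075, against 0.047 with an intercept only.
- Treatment by time, centred slopes, 1000 runs: 0.043 (correlation 0.5) and 0.059 (0.7).

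**4. Baseline tests.** The listed control variables are 7 + 3 = 10; time since stroke makes 11. Assuming independence, the chance of at least one significant factor is 1 − 0.95¹⁰ = 0.40, or 1 − 0.95¹¹ = 0.43.

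Simulation of a single endpoint (25 per arm, 10 factors of which 3 are prognostic, 8000 runs, covariate R² 0.3):

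- Power at a true effect of 0.8 SD: unadjusted 0.80, test-selected 0.79, prespecified 0.89.
- Type I error of the test-selected analysis: 0.042 (0.037 at R² 0.5).

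**The case against.** **The list is open.** It is introduced by e.g., the effects are called participant-level, and the power section mentions a mixed model for repeated measures. A participant intercept may well be intended, and an article need not spell out the covariance. This stands: the absence of a named structure is no finding in itself. What remains is that the terms the article does name are the wrong ones for the purpose it gives them.

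**A reader might infer that the primary test has a type I error of about 13%.** The documents do not support that. The primary question asks about greater improvement, which treatment by time answers when baseline is among the visits, and that contrast was near nominal even under the literal reading. The 13% needs no intercept, centred covariates (the plan says nothing about centring) and a test of level rather than change. That test cannot be dismissed altogether, because the fixed-effects sentence gives the time factor only 3 and 6 months. Read that way, treatment by time compares those two visits with each other, and the treatment effect on level carries the question.

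**A reader might infer that covariates in the primary model are chosen by significance test.** They are not. Selection is confined to secondary analyses, and RBU is a prespecified fixed effect in the primary model. The selected analysis is slightly conservative, so its cost is arbitrary adjustment and forgone power, not false positives.

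**A reader might add that the tests would catch a 0.5 SD imbalance only 41% of the time.** That figure is power against a true population difference, which randomization rules out. An observed 0.5 SD difference at 25 per arm gives t = 0.5/√(2/25) = 1.77, p about 0.08, and would not be flagged at 0.05.

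An unadjusted primary analysis is also valid. The case for adjustment is precision.

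**Conclusion.** The point holds as an error of specification with a limited effect on error rates. Three time-constant covariates are named as the random effects that account for repeated measures, which they cannot do properly, and they are missing from the mean.

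Fitted literally, the model gives a type I error of about 8 to 13% for an average post-baseline effect and near 5% for treatment by time. With a participant intercept and the covariates as fixed effects, both contrasts are near nominal. Until the random part is stated correctly, a reader cannot tell which of these models will be fitted.

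The baseline tests are poor practice in a secondary analysis: about 40% of trials would flag at least one chance difference, with no power gained. Prespecified covariates raised power from 0.80 to 0.89.

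These sizes rest on assumed correlations of 0.5 to 0.7, covariate R² of 0.3, independent factors and a 0.05 baseline test. The power comparison also assumes an effect of 0.8 SD. The gain from adjustment would shrink if the covariates predict outcome less well.

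**What to change.** 1. In the primary model, enter age, stroke severity and time from stroke to enrollment as prespecified fixed covariates, and delete them as examples of random effects.
2. State how the correlation is carried, in one of two forms. (a) Keep baseline, 3 and 6 months as outcomes, with a participant random intercept or an unstructured covariance over the three visits, and test treatment by time. (b) Model 3 and 6 months only, with baseline FONEFIM motor score as a fixed covariate and the correlation between the two visits modelled. A two-visit model without the baseline score would compare levels, not improvement.
3. Make the time factor in the fixed-effects sentence match the form chosen.
4. Replace the baseline significance tests with a descriptive baseline table, and use the same prespecified covariates in the secondary analyses.

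Cost: rewording, plus three model degrees of freedom (four if baseline FONEFIM is added) out of about 40 to 50 participants. Age and stroke severity are already listed as collected, and the plan already intends to use time since stroke.

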### Secondary Analyses

The secondary research questions are whether or not, over the 6-month study period, the participants who received the TR intervention have greater improvements in disability (disability component of the Late Life Functional Disability Instrument), falls related self-efficacy (Falls Self Efficacy Scale), and patient satisfaction (Stroke Specific Patient Satisfaction with Care Scale), compared to participants in the Usual Care group. Since these secondary outcomes are continuous and are measured at three time points for each participant, we will use linear mixed-effects models. A final secondary research question is whether the participants discharged from a VAMC with a RBU have greater improvements in function (physical function of the motor sub-scale of the FONEFIM) than participants discharged from a VAMC without a RBU. This latter question will be addressed in the primary analysis in which we will consider the interaction between treatment (TR intervention group or Usual Care group) and RBU (with or without).

None of the four Institutional Review Boards (at the Coordinating Center and the three individual study sites) that we obtained approval from nor the funding agency believed that a DSMB was required. Despite the fact that there was a decision to not have a formal DSMB at the outset of the trial, we did decide a priori to have an independent review of the safety of the participants during the trial. The PI of the study will do a mid-point review with regards to the prevalence of potential harms (hospitalizations, falls, stroke, death). At this mid-point review, the PI will conceal the codes from the rest of the study team of identification of participants. We track adverse events and protocol violations per standard IRB requirements. Adverse events, protocol violations, and anything out of the ordinary related to the protocol are reviewed in bi-weekly meetings with the PIs. Should there be any evidence of unusual adverse events, we will engage an external group to review these.

All Adverse Events regardless of seriousness or relationship to study procedures are entered on the database. The adverse event entered specifies the date of onset, action taken with respect to study procedures, corrective treatment/therapy given, outcome and his/her opinion as to whether the Adverse Event related to the intervention. The study coordinator at the Coordinating Center keeps a log of all adverse events, the date the event occurred and the date of the learned event. This log also differentiates such events by whether they are considered to be serious adverse events and whether or not they are related to the intervention. The study coordinator, in turn, reports the adverse events to the local institutional review board. The study coordinator also documents the participant withdrawals and determines and documents whether it is due to the intervention.

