#### Primary Research Question

Over the 6-month study period, does the TR group have greater improvement in physical function (motor subscale on the telephone version of the Functional Independence Measure [FONEFIM] [6,7] than a Usual Care group?

#### Secondary Research Question 1

Over the 6-month study period, does the TR group have greater improvement in disability (Disability component of the Late Life Function and Disability Instrument) [8] than a Usual Care group?

#### Secondary Research Question 2

Over the 6-month study period, does the TR group have greater improvement in falls-related self-efficacy (the Falls Self Efficacy Scale) [9] than a Usual Care group?

#### Secondary Research Question 3

Over the 6-month study period, does the TR group have greater improvement in patient satisfaction (the Stroke Specific Patient Satisfaction with Care Scale) [10] than a Usual Care group?

#### Secondary Research Question 4

Over the 6-month study period, do patients, regardless of intervention arm, discharged from Veterans Affairs Medical Centers (VAMC) with a RBU have greater improvements in function (motor sub-scale of the FONEFIM) than those from VAMCs without a RBU?

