## Methods

### Setting and Overall Study Design

This is a three-site, 2-arm, single-blinded RCT with enrollment at three VAMCs: 1) James A. Haley VAMC in Tampa, FL; 2) Atlanta VAMC, Decatur, GA; and 3) Durham VAMC, Durham, NC. The James A. Haley VAMC facility has a RBU, while the other two VAMCs do not have a RBU. However, the three facilities are otherwise fairly similar. The Richard L. Roudebush VAMC, Indianapolis, IN is the Coordinating Center. Eligible patients are randomized into the TR intervention or Usual Care groups. During the study, all participants receive usual care from their providers. The TR intervention is delivered over 3 months via home visits and telephone calls. Outcome assessments are conducted at baseline, 3-months and 6-months. Figure 1 outlines the study design.

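### Secondary question 4 asks for an RBU difference pooled over arms, but the plan answers it with the treatment-by-RBU interaction

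*Protocol article*

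**What the plan says.** Under Study Aims and Objectives, Secondary Research Question 4 reads "do patients, regardless of intervention arm, discharged from Veterans Affairs Medical Centers (VAMC) with a RBU have greater improvements in function", measured by the motor subscale of the FONEFIM over 6 months. Secondary Analyses restates it without reference to treatment, as "whether the participants discharged from a VAMC with a RBU have greater improvements in function". The sentence that follows then gives the analysis: "This latter question will be addressed in the primary analysis in which we will consider the interaction between treatment" and RBU.

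Primary Analyses describes the model to be used. "Fixed effects in the model will include treatment (TR or Usual Care), RBU, (with or without), time" at 3 and 6 months, "and the interactions between treatment and RBU and between treatment and time". So the listed terms are three main effects, treatment by RBU and treatment by time. RBU by time is not listed, and the article does not say whether the response is the raw score or the change from baseline.

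On the sites, Setting and Overall Study Design says that the Tampa "facility has a RBU, while the other two VAMCs do not have a RBU". Under Randomization, treatment is allocated within each site, and the number recruited at the RBU and non-RBU sites is left free.

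**The concern.** The question and the named test concern different quantities. The question is about a difference between two kinds of centre in how much patients improve, with the arms pooled. The interaction is about whether the benefit of TR over Usual Care is larger at one kind of centre than at the other.

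An analyst who follows Secondary Analyses literally can go wrong in two directions. A real RBU advantage shared by both arms could be reported as no difference. A significant interaction could be taken as evidence that RBU patients do better, when it says nothing about their average improvement. This is a stated assignment of a test to a question, so it is not a detail that a condensed article merely leaves to a fuller plan.

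**Working it through.** **1. The two contrasts.** Write m for mean improvement in each of the four cells: TR or Usual Care (T, U) by RBU or no RBU (R, N).

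- Question 4: Q = (m_TR + m_UR)/2 − (m_TN + m_UN)/2
- Named test: I = (m_TR − m_UR) − (m_TN − m_UN)

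If RBU adds d points in both arms, then m_TR = m_TN + d and m_UR = m_UN + d. This gives Q = d and I = 0 for any d. If RBU adds k/2 in the TR arm and takes k/2 away in the Usual Care arm, then Q = 0 and I = k. Either quantity can be present without the other.

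**2. Numerical illustration.** The article gives no power for question 4, so there is no stated figure to reproduce. Inputs:

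- 40 completers (20 per group) and 9.2 points, from Sample Size Determination and Statistical Power.
- SD 10.12, an assumption. The article gives only an unadjusted SD of 8.3 and not the adjusted one. A two-sided 5% t-test with 20 per group and 80% power detects a standardised difference of 0.909, and 9.2/0.909 = 10.12.
- 12 of the 40 at the RBU site, an assumption, because the split is left open.

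Standard errors with arms balanced within site:

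- SE(Q) = 10.12 × sqrt(1/12 + 1/28) = 10.12 × 0.345 = 3.49
- SE(I) = 2 × 3.49 = 6.98

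Simulated rejection rates (20,000 runs; linear model for change with arm, RBU and their interaction):

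| Truth | Named test (I) | Question 4 contrast (Q) |
|---|---|---|
| RBU adds 9.2 in both arms, no interaction | 5.0% | 73% |
| Interaction 18.4, no average RBU effect | 73% | 5.2% |

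The 5% does not depend on the assumptions, because I = 0 whatever the SD and the split. The 73% for Q does. By normal approximation at SD 10.12, it runs from 63% with 20% of patients at the RBU site to 82% with 50%. At SD 8.3 and 12 of 40, the ratio is 9.2/(8.3 × 0.345) = 3.21 and the power is about 89%.

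**3. Can the listed model supply Q?** This depends on the response.

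- *Change from baseline at 3 and 6 months.* The RBU effect averaged over arms is the RBU difference in improvement, so the model contains Q. With the interaction in the model, the RBU coefficient under reference coding applies to one arm only, so the averaged contrast has to be requested.
- *Raw score with baseline among the repeated outcomes.* Without RBU by time, the RBU and treatment-by-RBU terms are constant over time and cancel from any change. Q is then fixed at zero, and RBU by time is needed.

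The time levels given in Primary Analyses ("time (3-and 6 -months), and the interactions between treatment and RBU and between treatment and time") fit the first reading. The same paragraph and Secondary Analyses also speak of outcomes measured at three time points, which leaves the second open.

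**4. One RBU site.** RBU status coincides with one site against two. Suppose there is no RBU effect but sites differ in mean improvement with an SD of 1, 2, 3, 4 or 5 points (assumed; the article gives none). The Q contrast then rejects in 6.5%, 10.6%, 16.7%, 22.9% or 30.0% of runs.

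**The case against.** The strongest reply is that the planned model already lists RBU as a fixed effect in its own right, and that the 3- and 6-month time levels suit a change-from-baseline response. On that reading the arm-averaged RBU difference can be taken from the planned fit with no new term. The handling of baseline and the full term list may also stand in a fuller plan that is not shown. This stands. A reader might infer that the model cannot answer question 4 at all, and the article does not support that. What remains is that Secondary Analyses names the interaction, and no choice of response turns the interaction into the pooled comparison.

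A reader might also infer that sharing RBU status with a single site invalidates question 4. The article discloses the arrangement, the question is put as a comparison of centres without an explicit causal claim, and no analysis could separate the two. It calls for a caveat and no more.

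Finally, one might cite the low power of the interaction, since its standard error is twice that of the pooled contrast. Any figure for this rests on a back-solved SD and an assumed split, and the power of a test that does not address question 4 has no bearing on question 4.

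**Conclusion.** The point holds in a narrow form: Secondary Analyses ties question 4 to a contrast that does not answer it. With an RBU effect equal in both arms, the named test rejects at 5% whatever the size of that effect. This follows from the algebra and needs no assumption about SD or recruitment split. The simulated power and the false-rejection rates under site variation are illustrations that rest on the assumptions stated with them.

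The reach is limited. Question 4 is the last of four secondary questions in a 50-patient Phase II trial. The TR comparison is randomised within site and is not confounded by RBU status. The article does not say that a significant interaction would be reported as greater improvement in RBU patients. That is a risk of the wording, not a stated intention. The text should be corrected before question 4 is analysed.

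**What to change.** Reword Secondary Analyses so that question 4 is answered by the RBU versus non-RBU difference in change in motor FONEFIM from baseline to 6 months, averaged over arms, with its confidence interval. Either of two forms will do:

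- add RBU by time, if baseline is one of the repeated outcomes; or
- take the arm-averaged RBU effect, if the response is change from baseline.

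State which response is used. Adjusting for baseline as a covariate should not be substituted without comment. RBU status is not randomised, so if the two groups start at different levels, the baseline-adjusted difference can depart from the difference in mean improvement that the question asks for.

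Report treatment by RBU separately, as exploratory effect modification, and describe the question 4 result as a non-randomised comparison of one site with two others.

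The cost is one extra contrast or term, a wording change and a softer claim on question 4. No new data or design change is needed, and the primary comparison stays as it is.
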